## Abstract

**Background:**

While international guidelines recommend medication reviews as part of the management of multimorbidity, evidence on how to implement reviews in practice in primary care is lacking. The MultimorbiditY Collaborative Medication Review And Decision Making (MyComrade) intervention is an evidence-based, theoretically informed novel intervention which aims to support the conduct of medication reviews for patients with multimorbidity in primary care. Our aim in this pilot study is to evaluate the feasibility of a trial of the intervention with unique modifications accounting for contextual variations in two neighbouring health systems (Republic of Ireland (ROI) and Northern Ireland (NI)).

**Methods:**

A pilot cluster randomised controlled trial will be conducted, using a mixed-methods process evaluation to investigate the feasibility of a trial of the MyComrade intervention based on pre-defined progression criteria. A total of 16 practices will be recruited (eight in ROI; eight in NI), and four practices in each jurisdiction will be randomly allocated to intervention or control. Twenty people living with multimorbidity and prescribed ≥ 10 repeat medications will be recruited from each practice prior to practice randomisation. In intervention practices, the MyComrade intervention will be delivered by pairs of general practitioners (GPs) in ROI, and a GP and practice-based pharmacist (PBP) in NI. The GPs/GP and PBP will schedule the time to review the medications together using a checklist. Usual care will proceed in practices in the control arm. Data will be collected via electronic health records and postal questionnaires at recruitment and 4 and 8 months after randomisation. Qualitative interviews to assess the feasibility and acceptability of the intervention and explore experiences related to multimorbidity management will be conducted with a purposive sample of GPs, PBPs, practice administration staff and patients in intervention and control practices. The feasibility of conducting a health economic evaluation as part of a future definitive trial will be assessed.

**Discussion:**

The findings of this pilot study will assess the feasibility of a trial of the MyComrade intervention in two different health systems. Evaluation of the progression criteria will guide the decision to progress to a definitive trial and inform trial design. The findings will also contribute to the growing evidence-base related to intervention development and feasibility studies.

**Trial registration:**

ISRCTN Registry, ISRCTN80017020. Date of confirmation is 4/11/2019.

**Supplementary Information:**

The online version contains supplementary material available at 10.1186/s40814-022-01018-y.

## Introduction

Multimorbidity, the co-occurrence of two or more long-term conditions, is frequently encountered by general practitioners (GPs), with approximately one in four adults living with multimorbidity, and half of older adults diagnosed with three or more chronic conditions internationally [1]. Prescribing is one of the most complex and important considerations of multimorbidity management. Polypharmacy describes the prescription of multiple medications, but consensus is lacking on the threshold number of medications that should be used to define polypharmacy. Although five or more medications are commonly used, more recent studies have used a cutoff of ten or more medications to indicate patients at greater risk of adverse events from their medications [2, 3]. Certainly, higher numbers of medications are associated with a greater risk of preventable drug-related morbidity [4, 5], and the use of multiple medications may impose a burden on individuals, reducing medication adherence [6]. The prevalence of polypharmacy is strongly associated with the number of conditions a person has, for example, a large primary care study conducted in Scotland showed 42% of patients with six or more conditions were prescribed 10 or more medications [7]. However, using multiple medications for the control of chronic disease may also benefit the patient by reducing morbidity and improving quality of life.

A range of factors have been identified as contributing to the complexity of prescribing for general practitioners (GPs) in the context of multimorbidity and the resultant challenges in clinical decision-making [8]. For example, specialists initiate many of the medications taken by patients with multimorbidity, but the responsibility for repeat prescribing of these medications lies with primary care [6]. Several studies show the dilemmas experienced by GPs who query the ongoing appropriateness of repeat medications, which is further complicated by suboptimal communication between primary and secondary care [9, 10]. In addition, drawing on treatment guidelines for prescribing decisions in multimorbidity is often unhelpful or counterproductive as guidelines are designed for single diseases [8].

The prevalence of multimorbidity and polypharmacy continues to grow [11]. Yet, there is a lack of intervention research in this area to guide the effective management of medications in primary care [12]. Individual structured medication reviews are recommended by the National Institute for Health and Care Excellence (NICE) as key in the management of multimorbidity [13], but evidence shows such reviews frequently do not occur [14]. Medication review is a modifiable and potentially impactful behavioural target in multimorbidity management in primary care. The MultimorbiditY Collaborative Medication Review And Decision Making (MyComrade) intervention was developed to address barriers to medication reviewing by GPs, through a series of studies conducted according to the Medical Research Council (MRC) Framework for the development and evaluation of complex interventions and using the Behaviour Change Wheel [15–17]. The Capability, Opportunity, Motivation – Behaviour (COM-B) model and Behaviour Change Technique (BCT) Taxonomy [18] are key features of the Behaviour Change Wheel system, utilised in the development of this intervention. The development and key features of MyComrade are outlined in Table 1 and described in detail elsewhere [15].

**Table 1 Tab1:** MyComrade intervention: barriers to medication reviewing and operationalisation of MyComrade BCTs

Behavioural analysis using COM-B: what are the barriers to medication review in multimorbidity?		Selected behaviour change technique and definition	Original operationalisation of BCTs in the MyComrade intervention	Revised operationalisation of BCTs in the MyComrade intervention, based on the findings of the feasibility study [19] and contextual requirements
Uncertainty about most valuable medications.	Psychological capability	3.2 Social support—practical *Advise on, or provide practical help (e.g. colleagues) for the performance of behaviour*	Two GPs collaboratively conduct a medication review	Two GPs or a GP and PBP collaboratively conduct a medication review
Perceptions related to patient unwillingness to stop long-term medications.	Social Opportunity			
Lack of time to properly review medications.	Physical opportunity	12.2 Restructuring social environment *Change or advise to change the social environment in order to facilitate performance of the wanted behaviour* 1.4 Action planning *Prompt detailed planning of performance of behaviour (must include at least one of frequency, context, duration, intensity)*	Plan active medication reviews	Plan active medication reviews
An instinct to maintain the status quo.	Automatic motivation	7.1 Prompts/cues *Introduce environmental or social stimulus for the purpose of prompting or cueing behaviour*	Use of prescribing checklist	Use of prescribing checklist
Fear of negative consequences.	Reflective motivation	10.7 Self-incentive *Plan to reward self in the future if and only if there has been an effort and/or progress in performing the behaviours*	Annual professional appraisal contribution	Annual professional appraisal contribution
Opportunity cost of reviewing medications.				
Based on the findings of the non-randomised feasibility study [19], an additional BCT was added to the MyComrade intervention to provide the necessary support to address the opportunity cost of reviewing medications.	Reflective motivation	10.1 Material incentive (behaviour) *Inform that money, vouchers or other valued objects will be delivered if and only if there has been an effort and/or progress in performing the behaviour*		Financial reimbursement for review completion *All practices:* €500/£430 for the administration associated with recruiting patients *Intervention practices only:* • €100/£86 for completing the intervention introduction session • €50/£43 per completed medication review

The aim of the MyComrade intervention is to support GPs to conduct medication reviews for patients with multimorbidity with a view to optimising the medication regimen and minimising potentially inappropriate prescribing [15–17]. As recommended by the MRC Framework, the feasibility of MyComrade was tested in a non-randomised qualitative feasibility study [19]. The findings showed MyComrade’s acceptability to GPs and that all the medication reviews conducted produced recommendations for medication optimisation. However, participating GPs felt that the sustainability of this approach would require an incentive mechanism, due to the time, personnel demand and opportunity cost of this activity.

The findings of the feasibility study justified proceeding to a randomised pilot trial to address remaining uncertainties and guide the decision to progress to a definitive trial of the intervention [16]. In particular, a pilot would allow testing of the MyComrade intervention and study procedures on a small scale [20] and inform important refinements to facilitate the conduct of a robust and transparent definitive trial [16, 21].

A funding opportunity arose for a pilot trial to be conducted across the Republic of Ireland-Northern Ireland border. This opportunity required that unique modifications would be made to the MyComrade intervention to account for the contextual differences in the Irish and Northern Irish health systems. The original MyComrade intervention, developed in the Republic of Ireland (ROI), included collaborative medication review by two GPs. In Northern Ireland (NI), the majority of primary care practices have access to a pharmacist, as a result of a Primary Care Pharmacy scheme launched in 2016 [22] ([name], personal communication, June 4, 2020), with a key responsibility for conducting medication reviews [23]. Therefore, the MyComrade collaborative medication reviews will take place in Northern Ireland with a GP and a practice-based pharmacist (PBP). Additionally, based on the findings of the feasibility study [16], the MyComrade intervention was further refined by adding a behaviour change technique (i.e. material incentive) to address the high opportunity cost of medication reviewing.

The aim of this study is to evaluate the feasibility of a trial of the modified MyComrade intervention, including cross-border comparison, using a pilot cluster randomised controlled trial (cRCT). The primary objective is to determine the feasibility of a definitive trial of the MyComrade intervention, focusing on recruitment, retention and fidelity of intervention implementation. The secondary objective is to select suitable outcome and cost-effectiveness measures for use in a definitive trial. This study will also enable the assessment of the feasibility of MyComrade in two different health systems, producing data on the adaptability and potential generalisability of the intervention.

## Methods

### Trial design

A parallel-group, pilot cRCT of the MyComrade intervention will be conducted, where GP practices are the units of randomisation (the clusters), and individual patients with multimorbidity, prescribed 10 or more medications, are the units of analysis (the participants). Figure 1 illustrates the study design. The trial will be conducted based on best practice guidelines for conducting a process evaluation [24] and reported according to the CONSORT guidelines, adapted for pilot studies [21] and Standard Protocol Items: Recommendations for Interventional Trials (SPIRIT) 2013 Statement [25]. A completed SPIRIT checklist is provided in Additional file 1.

**Fig. 1 Fig1:**
[figure not shown]
MyComrade study design

A total of 16 practices will be recruited (eight in ROI; eight in NI), and four practices in each jurisdiction will be randomly allocated to the intervention or control arms. Patients with multimorbidity who are prescribed 10 or more repeat prescription medications will be identified in each practice. From each practice, 20 patients with multimorbidity will be recruited, providing a total of 320 participants. The list of 20 consented patients from each practice will be shared with participating GPs/PBPs. In the intervention arm, pairs of GPs/GP and PBPs will use the MyComrade intervention and will be asked to complete collaborative medication reviews before the 4-month follow-up time point. ROI pairs will be GP-GP, and NI pairs will be GP-PBP. Control practices will proceed with usual care. Participant data will be collected from primary care practice records and postal questionnaires sent to participants at baseline before randomisation takes place and at 4 and 8 months after the date of randomisation. Qualitative interviews to assess the study feasibility and acceptability and to explore experiences related to multimorbidity management will be conducted with a purposive sample of GPs and PBPs participating in the study, practice administration staff and patients.

A Public and Patient Involvement group has been established, involving four adults (two women and two men) from both NI and ROI and living with multimorbidity. This group have provided input into the patient recruitment materials, and qualitative interview guides, and will provide input into the interpretation of the qualitative findings and methods for disseminating the study findings. The establishment and running of this group as research partners in this study are guided by the PPI Ignite @ NUI Galway programme office, part of a national PPI programme funded by the Health Research Board in Ireland.

### Participants

#### Eligibility criteria

##### Primary care practices

Eligible practices in ROI will have at least two GPs willing to conduct medication reviews. In NI, at least one GP and one PBP must be willing to conduct medication reviews for a practice to be eligible. Practices currently involved in other research involving patients with multimorbidity will not be eligible.

##### Patients

Eligible patients must be living with multimorbidity and prescribed ten or more medications. Patients will not be eligible for this study if they are under 18 years old at the time of medical record review, are pregnant, undergoing terminal illness care or have cognitive or learning disabilities that would prevent them from completing the study activities.

### Study setting

This study will take place in primary care practices in NI and ROI. The populations of these jurisdictions are similar in terms of ethnicity, with the majority of people in both regions being white [26] and with similar socioeconomic gradients [27]. GPs in both jurisdictions work as independent contractors [28], but the health systems differ in important ways, principally that the system in ROI is a mixed public and private system, while the system in NI is publicly funded [29]. In ROI, patients are means-tested to determine eligibility for a medical card, which entitles them to GP care, medications and other medical services free at the point of access [28]. In 2019, 32.4% of the ROI population had a medical card [30]. Patients without a medical card pay out of pocket for their medical care and medications. All patients aged over 70 years get free access to GP care but only those with medical cards are eligible for free medications. In NI, GP services are free at the point of access to all patients [31].

Since 2016, most GP practices in NI have access to a PBP, although the hours and role of the PBP will vary depending on the size and specific needs of the practice. Tasks performed by the PBP may include medication reviews and medication reconciliation following discharge from the hospital [22].

### Recruitment

Primary care practices will be contacted by the research team via several communication pathways: the Northern Ireland Clinical Research Network (NICRN) Primary Care network, the HRB Primary Care Clinical Trials Network of Ireland (HRB PC CTNI), ROI and NI business directories, local GP education events and meetings and local GP social media groups. Practices will be sent information on the study and asked to express an interest in taking part. Interested practices will be contacted by a member of the research team to further discuss the study. Before recruitment, each practice will be provided with instructions and asked to run a search in their record system to assess the number of potential participants based on their number of prescription medications (target > 60 potentially eligible patients per practice). Practices will be informed at the outset of the material supports associated with participation in the study and details of the implementation of the intervention (Table 1).

Eligible patients will be identified in NI and ROI using electronic record search procedures. These search procedures will be modified to take into account the different electronic practice record systems used in both jurisdictions. In the ROI, a search procedure developed and tested in another Irish primary care multimorbidity trial [32] will be used to identify eligible patients. In NI, a similar search procedure will be developed by the study team and pilot tested for the two main electronic practice record systems there. To comply with the General Data Protection Regulation (GDPR), only practice staff members will review the list of eligible patients generated by the search procedure and apply the study eligibility criteria. Eligible patients will receive a recruitment pack, consisting of an invitation to participate in the study, a participant information leaflet, and a consent form. Recruitment packs will be provided by the study team but will be addressed and posted by the practice teams, to adhere to GDPR. To minimise selection bias, patients will be randomly selected from the list of eligible patients, and recruitment packs will be sent out until 20 patients from each practice consent to participate.

### Intervention

The MyComrade intervention is a complex intervention, which aims to increase the behaviour of active medication review. MyComrade initially involved five components (Table 1); a sixth component material incentive was added based on the results of the first feasibility study of this intervention [19]. The intervention is described using the Template for Intervention Description and Replication (TIDieR) Checklist [33] in Additional file 2.

MyComrade will be implemented in intervention practices following recruitment of participants, baseline data collection and practice randomisation. The research team will deliver a brief introduction session on the intervention. The introduction session will be audio-recorded to allow independent fidelity assessment, in terms of content and duration. The GP research fellow with the NI- and ROI-based study teams (LMQ and SM) will contact each intervention practice 3 and 6 weeks after this session to gauge progress in terms of medication review completion and address any study-related questions.

Participating GPs and PBPs will be given the list of eligible patients from their practice who consent to take part. GP/GP and PBP pairs will schedule a time to meet each other to conduct each collaborative medication review, using a medication review checklist to guide the discussion. The medication review checklist was adapted from the “NO TEARS” tool for a medication review [34], originally designed for doctor-patient medication reviewing. This seven-item tool was selected due to its simplicity and was described by GPs in the feasibility study for the MyComrade interventions as a helpful guide for a medication review [19]. The earlier feasibility study suggested that reviews take between 10 and 30 min each. GP/PBPs will scan the completed checklist into the participant’s practice record, highlighting any potential options for medication changes and discussing these with the participant prior to making changes.

### Outcomes

The primary outcomes are the feasibility of practice recruitment, patient recruitment, practice retention, patient retention and feasibility of intervention implementation. Secondary outcomes are completion of medication reviews (GP/PBP outcome), treatment burden and quality of life (patient outcomes) and number of prescribed medications, changes in prescribed medications, deprescribing and indicators of potentially inappropriate prescribing (prescribing outcomes). The indicators of potentially inappropriate prescribing were adapted from the set of evidence-based, validated prescribing safety indicators developed in the PINCER trial [35]. The secondary outcomes will be used to inform the choice of primary outcome should we proceed to a definitive trial at a later stage. The logic model in Additional file 4 illustrates the intervention components, proposed mechanisms of impact of each component, contextual factors and outcomes. The logic model was designed based on guidance from Moore et al. [36].

Data will be collected on GP practice demographic information and patient demographic information and healthcare utilisation. Additional file 3 provides a summary of the variables measured in this study and the data source for each. The secondary outcomes will be assessed at baseline and at 4 and 8 months after randomisation of practices. The variability, consistency, response rates, success of data collection methods and data completeness for each outcome will be determined to understand the feasibility and acceptability. These findings will help to determine the primary outcome(s) for a future definitive trial.

#### Progression criteria

The progression criteria for this study (Table 2) were developed based on Avery et al.’s Top Ten Tips for guiding the decision to progress from a pilot to a definitive trial, focusing on key acceptability and feasibility variables [37]. Several rounds of discussions were held within the study team to draft the criteria outlined in Table 2. Discussions were guided by existing literature, study team experience, the pilot study design and potential barriers and facilitators to practice and patient involvement. As part of the process evaluation within this study, qualitative and quantitative data will be collected for the investigation of the following outcomes: feasibility of practice recruitment, feasibility of patient recruitment, feasibility of practice retention, feasibility of patient retention and feasibility of intervention implementation.

**Table 2 Tab2:** MyComrade progression criteria

	Go—proceed with RCT	Amend—proceed with changes	Stop—do not proceed unless changes are possible
**1. Feasibility of practice recruitment** Can 16 practices be recruited to take part in 3 months (8 practices in NI and 8 in ROI)?	If > 14 practices are recruited to take part in 3 months	If > 14 practices are recruited, but it takes longer than predicted (e.g. 3–6 months)	Unable to recruit practices
**2. Feasibility of patient recruitment** Can 20 patients per practice (total *N* = 320) be recruited?	If 20 patients are recruited in one month per practice; a total of 320 (100%)	If 10–19 patients are recruited in one month per practice; a total of 160–319 (50 to < 100%)	If < 10 patients are recruited in one month per practice; a total of < 159 (50%)
**3. Feasibility of practice retention** Can > 14 practices be retained in the study until completion?	> 14 (88%) retained	> 12 (75%) retained	< 12 retained
**4. Feasibility of patient retention** Can at least 80% of recruited patients be retained in the study until completion?	> 256 (80%) retained	224–255 (70–80%) retained	< 224 retained
**5. Intervention implementation**	Delivery of intervention judged strongly feasible by qualitative data	Delivery of intervention judged feasible by qualitative data	Delivery of intervention judged possibly feasible by qualitative data

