### Sample size

As this is a pilot study, a formal sample size calculation was not done [38]. This study aims to recruit 16 primary care practices (eight in NI and eight in ROI) and 20 patients per practice (*N* = 320), based on recommendations from Eldridge et al. [20] and the CONSORT guidance [21] on the minimum number of clusters required in pilot and definitive cRCTs, respectively. The aims of this pilot cRCT are to investigate feasibility and acceptability and to identify the most suitable primary outcome(s) for a definitive cluster randomised trial. The estimates from this pilot trial will be used to calculate the sample size needed using the methods outlined by Rutterford et al. [39].

Based on an assessment of the number of practices and practice sizes in the region, we will invite 50 patients per practice and, a priori, have defined a success criterion as 40% of the total number of participants invited to be recruited to the research evaluation (approximately 20 patients per practice).

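### The patient-recruitment Go threshold is the full planned sample: it clashes with the practice-recruitment Go threshold and can disagree with the separate 40%-of-invited success criterion

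*Protocol article*

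**What the plan says.** Four statements in the protocol article bear on this point.

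- **Planned size.** The Sample size section says "This study aims to recruit 16 primary care practices (eight in NI and eight in ROI) and 20 patients per practice". The Trial design section gives the same total: "From each practice, 20 patients with multimorbidity will be recruited, providing a total of 320 participants".
- **Table 2, row 2 (patient recruitment).** Go is "If 20 patients are recruited in one month per practice; a total of 320 (100" per cent). Amend is "If 10–19 patients are recruited in one month per practice; a total of 160–319 (50 to < 100" per cent). Below that is Stop.
- **Table 2, row 1 (practice recruitment).** Go is "If > 14 practices are recruited to take part in 3 months", so 15 or 16 practices qualify.
- **Number invited.** The Sample size section says "we will invite 50 patients per practice and, a priori, have defined a success criterion as 40% of the total number of participants invited" should be recruited, glossed as "approximately 20 patients per practice". The Recruitment section says "recruitment packs will be sent out until 20 patients from each practice consent to participate", after a record search with a target of more than 60 potentially eligible patients per practice.

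Patient recruitment is one of the primary feasibility outcomes. According to the abstract, the progression criteria are to guide the decision on a definitive trial. The Study status section reports that recruitment of practices and patients was already complete at submission.

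**The concern.** A progression rule should give one verdict for one set of data. Here the verdict can depend on which section is consulted.

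- Row 2's total presupposes all 16 practices, whereas row 1 counts 15 as full success.
- The 40% criterion is described as a priori, but it sits outside Table 2. It is a proportion of those invited, while row 2 is a count within one month.
- Because the number invited is fixed in one section and open in another, the proportion and the count can separate.

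With two success rules on record and nothing to say which governs, the verdict on a primary outcome could be chosen after the data are seen. In addition, if packs go out until 20 consent, reaching 20 says little about uptake. Only the one-month limit or an exhausted list could then separate Go from Amend. Yet uptake per invitation is what a definitive trial needs in order to plan its mailing.

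**Working it through.** **Inputs from the protocol article:** 16 practices; 20 patients per practice; row 1 Go above 14 practices; row 2 Go at 320 and Amend at 160–319; 50 invitations per practice; success at 40% of invited; more than 60 potentially eligible patients per practice as a target.

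**1. The plan's own figures reproduce.** 16 × 20 = 320. Also 50 × 0.40 = 20 per practice, and 16 × 50 × 0.40 = 320. At exactly 16 practices and 50 invitations each, the 40% criterion and row 2's total coincide.

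**2. Tolerance in row 2.** Go needs 320/320 = 100%. One practice at 19 gives 15 × 20 + 19 = 319, which is Amend. By contrast, row 1 accepts 15/16 = 93.75%.

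**3. Row 1 against row 2.** Fifteen practices at 20 each give 15 × 20 = 300, or 300/320 = 93.75%. That is Go in row 1 and Amend in row 2. Reaching 320 would need 320/15 = 21.3 per practice, which sending packs only until 20 consent does not allow. This step needs no model.

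**4. Row 2 against the 40% criterion.**

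| Outcome | 40% of invited | Row 2 |
|---|---|---|
| 16 practices, 320 of 800 | 40%: met | Go, if every practice has 20 within a month |
| 15 practices, 300 of 750 | 40%: met | Amend (300) |
| 16 practices, each 20 of 60 | 33%: not met | Go, if within a month |
| 16 practices, each 20 of 80 | 25%: not met | Go, if within a month |

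The last two rows can arise only if packs continue beyond 50, as the Recruitment section allows. The 80 is an illustration and needs an eligible list at least that long.

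**5. How hard Go is to reach.** The article gives no expected consent rate and no between-practice variation, so this step rests on assumptions: independent consent, the same rate in every practice, and the one-month limit ignored. With n invitations and consent rate p, the chance that one practice reaches 20 is P(Bin(n, p) ≥ 20). For all 16 practices it is that value to the power 16. At p = 0.40:

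| Reading | One practice reaches 20 | All 16 reach 20 |
|---|---|---|
| 50 invitations | 0.5535 | 0.5535^16 = 0.00008 |
| 60 invitations | 0.883 | 0.14 |
| 80 invitations | 0.998 | 0.97 |

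At p = 0.45 and 0.50, the all-16 figure is 0.03 and 0.38 with 50 invitations, and 0.67 and 0.95 with 60.

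If 50 are invited with no cap at 20 and only the total counts, P(Bin(800, 0.40) ≥ 320) = 0.51. At p = 0.45 this becomes 0.998.

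**The case against.** **Go is practically unreachable.** A reader might infer this from the 0.00008. The documents do not support it as a general statement. That figure needs exactly 50 invitations, a true rate of exactly 40%, and every practice at 20. The Recruitment section lets packs continue, and 60 or 80 invitations give 0.14 or 0.97. Row 2 can also be read as an average plus a total, which gives 0.51 if practices may exceed 20. Moreover, 40% is stated as a success threshold, not a forecast, and any threshold is met about half the time when the truth lies on it.

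**Sending packs until 20 consent contradicts the Go rule.** A reader might infer this too, but it does not. It is a route to 20 per practice. Its conflict is with the fixed 50 in the Sample size section.

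**The consequence is limited.** Missing Go leads to Amend, which still proceeds with changes, and the criteria guide the decision without dictating it. A demanding Go threshold is a legitimate choice, and rows of a progression table may give different verdicts. This stands, and it limits the seriousness of the point. It does not explain why row 2's total ignores row 1's own success range.

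**The consent rate is not ignored.** It is an a priori criterion in the Sample size section, and recruitment rates will be collected. That also stands. The defect is that the criterion is outside Table 2 and has no stated precedence.

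**Recruitment is complete.** Replacing the rule now would be a post hoc change, and invitations cannot be rerun. This stands and shapes the fix.

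**Conclusion.** The point holds as an inconsistency in a decision rule for a primary outcome. Three parts follow from the text and simple arithmetic:

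- Row 2's Go is the whole planned sample, with no tolerance.
- Fifteen practices are Go in row 1 but yield at most 300 at 20 each, which is Amend in row 2.
- The 40% criterion agrees with row 2's total only at 16 × 50 invitations and can disagree in either direction elsewhere.

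The number invited is also fixed in two incompatible ways, and under the open-ended one the count of 20 does not measure uptake.

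The chance of Go cannot be given as a single number. At 40% consent it runs from 0.00008 to 0.97 for 50 to 80 invitations when every practice must reach 20, and it is 0.51 for an uncapped total from 800. All of these rest on the binomial model with equal rates and, apart from the invitation count, ignore timing. The practical effect is a possible shift between Go and Amend. None of the examples here leads to Stop.

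**What to change.** 1. In row 2, express the total relative to the practices actually recruited: 20 × number of practices for Go, with the Amend band scaled in the same way. With 15 practices, Go is 300 and Amend runs from 10 × 15 = 150 to 299. Row 2 then agrees with row 1.
2. Declare one governing recruitment rule and put it in Table 2. The already prespecified 40%-of-invited criterion is suitable, with every pack posted, top-ups included, in the denominator. Keep the number recruited per practice within one month beside it, since achievable cluster size matters for the definitive trial and a percentage alone would lose it. The 40% criterion has only one threshold, so say what separates Amend from Stop.
3. Reconcile the Recruitment and Sample size sections on the number invited: state whether 50 was a fixed number, a first mailing or an expectation.
4. Because recruitment is complete, report the result under both rules as published, and label the reconciliation as a dated clarification made after recruitment, not as a replacement criterion.

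The cost is a change of wording in Table 2 and two sections, plus a count of packs posted per practice. The downside is that the verdict under the declared rule may be less favourable, for example if many top-up packs were needed.
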